### **Analysis plan**

#### **A] General population**

We will calculate the frequency of characteristics of survey participants. The reported occupations will be categorised into high and low risk considering the potential risk of exposure to known or unknown COVID-19 case.

We will estimate the seroprevalence of SARS-CoV-2 infection along with 95% confidence intervals using appropriate sampling weights and considering the cluster sampling used for the survey. We will define an antibody positive case as an individual whose sera tested positive on either of the two assays. Hence the sero-prevalence estimated will be based on presence of either N antibodies or S1-RBD antibodies. The final prevalence estimates will be calculated after adjusting for the IgG test performance characteristics of both assays.

We will use the survey data analysis module in STATA software (StataCorp LLC, Texas, USA).

We will separately estimate the seroprevalence of infections only among the adults. In order to maintain comparability with the previous surveys, we will randomly select one adult survey participant per household from the survey database.

We will estimate proportion of individuals with COVID-19 vaccination along with 95% CI. We will also estimate the seroprevalence with 95% CI for SARS-CoV-2 infection by age, sex, locality, occupation, symptom status, contact history, RT-PCR testing and confirmation status.

We will estimate the infection-to-case ratio as the number of individuals with SARS-CoV-2 infection (as per IgG detection) compared to the number of RT-PCR reported cases of COVID-19. We will apply the seroprevalence to the total population above 10 years projected for the year 2020 using 2011 census data to estimate the number of infections in the country. The published literature indicates that the IgG antibodies against SARS-CoV-2 infection start appearing by the end of first week, and most cases are IgG positive by the end of the second week (10). We will consider the number of reported COVID-19 cases 15 days and one week before the initiation of serosurvey to estimate the plausible range of the number of infections. We will estimate the range of the infection fatality ratio (IFR) assuming a three-week lag time from infection to death (11,12)

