## **Population-based serosurvey to estimate prevalence of SARS-CoV-2 antibodies in India: Fourth survey, June - July 2021**

India is witnessing a second wave of SARS-CoV-2 infections from February 2021, spread across majority of states of India (1). As of May 29, 2021, India had reported around 25 million cases and more than 3,00,000 deaths (2). The first round of national serosurveillance was conducted from May 11, 2020, to June 4, 2020, among adults in randomly-sampled 700 clusters selected from 70 districts of 21 Indian states. The population-weighted seroprevalence after adjusting for test performance was 0.73% (95% CI: 0.34-1.13). The second round of nationwide serosurvey was conducted between 17 August and 22 September 2020 among individuals aged 10 years and above in the same clusters from 70 districts of 21 states (3). The findings indicated an overall seroprevalence of around 7%, with a ten-fold rise in adult prevalence between May and August 2020. It also indicated a substantial transmission in rural areas with the seroprevalence continuing to be higher in urban slum and non-slum areas (4).

ICMR conducted the third population-based serosurvey among individuals aged 10 years and above and health care workers between Dec 18, 2020 and Jan 6, 2021 in the same 700 villages or wards from 70 districts in 21 states selected for the first and second serosurveys. In the third serosurvey, prevalence was estimated based on the presence of both IgG antibodies against SARS-CoV-2 S1 protein of the receptor binding domain (S1-RBD) and nucleocapsid (N) protein of SARS-CoV-2 while in second serosurvey prevalence was based on IgG antibodies nucleocapsid (N) protein of SARS-CoV-2. The weighted and assay characteristic adjusted seroprevalence among general population was 24.1 (95%CI: 23.0% to 25.3%) The survey indicated that three fourth of the population were still susceptible and a higher sero-prevalence of SARS-CoV-2 infection in urban areas compared to the rural areas (5). Apart from the nationwide serosurveys, several cities and states conducted serosurveys. Metropolitan cities like Delhi, Mumbai, Pune, Chennai, Ahmedabad, Hyderabad have reported seroprevalence ranging between 17.6% and 56% at different timepoints (5).

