India started COVID-19 vaccination with BBV152 vaccine (Covaxin; Bharat Biotech) and ChAdOx1 nCoV-19 vaccine (COVID-19 Vaccine AstraZeneca) since January 16, 2021 under Emergency Use Authorization for the health care workers. The vaccination strategy was expanded for frontline workers in February 1, 2021 for frontline workers. In Phase 2 individuals above 60 years old and above 45 years old with specified comorbidities

became eligible for vaccination from March 1, 2021 followed by Phase 3 for all above 45 years of age from April 1, 2021. And finally Phase 4 for all above 18 years of age began on May 1, 2021 (6). Around 44 million individuals have received two doses while 160 million have received at least one dose of vaccine as on May 29, 2021 (7).

Population-based sero-epidemiological studies measure the presence of antibodies against SARS-CoV-2 (natural and vaccine induced) in different age groups. Repeated cross sectional serosurveys conducted in the same geographical location provide estimates to monitor trends over a period of and provide information valuable for the public health decision makers to design and revise containment strategies (8). The earlier serosurveys were conducted among individuals aged 10 years and above and seroprevalence among children below 10 years is still unknown. SARS-CoV-2 poses a high occupational risk to healthcare workers who are at the forefront of managing COVID-19 cases in hospital settings. The third serosurvey indicated seroprevalence around 25% among the HCWs. Also, the HCWs were prioritised for COVID-19 vaccination in the first phase of vaccine rollout in India owing to higher risk of exposure to infected persons.

In this context, it is proposed to conduct fourth round of serosurveillance to determine the prevalence of SARS-CoV-2 antibodies in the community and health care workers as per change in epidemiology and public health response to the epidemic in the country.

The objectives of the fourth survey are:

1. Estimate the prevalence of SARS-COV-2 antibodies among (a) children aged 6-17 y and (b) adults in the general population, at the national level
2. Estimate the prevalence of SARS-COV-2 antibodies among healthcare workers at the national level

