### **Sample size**

#### A] General population

We plan to enrol 28,000 individuals (19,600 individuals in the age group  $\geq 18$  years, 5600 children in the age group of 10-17 years and 2,800 children in the age group of 6-9 years) across the country by allocating a minimum of 400 individuals to each of the 70 districts that were included in the earlier survey. We have divided the overall sample size of 28,000 in the above-mentioned age groups as per age structure of the population (Census 2011).

The sample size assuming a seroprevalence of 30%, with 10% relative precision, for 95% CI and design effect of 2 would be 1792 for children in the 6-9 age group. The required sample size is sufficient to estimate prevalence for each age group. However, in order to have a sufficiently large sample for a national level survey, we will keep the same overall sample size for the fourth serosurvey.

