### **Sampling method**

#### A] General population

We will select 10 clusters (villages in rural areas and wards in urban areas) for each of the district by Probability proportional to size sampling. In each of the selected village/ward, we will select four random locations. In each location, the survey team will choose a random start household and visit consecutive households until 7 individuals from age-group  $\geq 18$  years, 2 children in the age group of 10-17 years and 1 child in the

age group of 6-9 years are enrolled. All household members, 6 years and older, will be included. Within each cluster, 40 individuals (28 individuals from  $\geq 18$  years, 8 children in the age group of 10-17 years and 4 children in the age group of 6-9 years) will be included for the survey. Individuals with history of laboratory confirmed SARS-CoV-2 infection by RT-PCR and/or rapid antigen test will not be excluded. SARS-CoV-2 cases in home isolation will not be included in the survey.

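### The variance statement points to the 700 villages/wards, not the 70 districts they are nested in, so the national confidence interval could be too narrow

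*Combined protocol and SAP*

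**What the plan says.** The first objective is a prevalence estimate for children and for "adults in the general population, at the national level".

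The sample is nested. Under Sample size, A] General population, the plan keeps the earlier districts, "allocating a minimum of 400 individuals to each of the 70 districts that were included in the earlier survey". Under Sampling method, A] General population, it states: "We will select 10 clusters (villages in rural areas and wards in urban areas) for each of the district by Probability proportional to size sampling". Four random locations are then chosen in each village or ward and consecutive households are visited, to give "Within each cluster, 40 individuals". The introduction describes the first survey's sample as "randomly-sampled 700 clusters selected from 70 districts of 21 Indian states". In both places a cluster is a village or ward, and the district is never called one.

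The only variance statement for the main result is in Analysis plan, A] General population. It promises appropriate weights and an interval "considering the cluster sampling used for the survey", computed with Stata's survey module. It does not name the PSU, the stages or the strata. The documents do not say how the 70 districts were chosen, or whether states or anything else served as strata.

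**The concern.** The survey module uses whatever PSU it is given. The protocol's own vocabulary leads to the village or ward, which is the second stage of selection. Villages in one district share much of their epidemic history. If prevalence differs between districts, the ten villages from one district are correlated, and 700 units do not carry 700 units' worth of national information. A village-based variance counts the between-district component as if it were averaged over 700 independent draws instead of 70, so only a tenth of its contribution is kept.

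At stake is the coverage of the headline national interval. The adult, child and subgroup intervals are affected too, though less so where few people per village contribute.

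**Working it through.** **Plan's own figure.** For ages 6-9 the plan uses prevalence 30%, relative precision 10%, 95% confidence and design effect 2: n = 2 × 1.96² × 0.70 / (0.30 × 0.10²) = 1,792.7. This agrees with the stated 1,792. The totals also agree: 70 × 10 × 40 = 28,000.

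**Inputs.** From the protocol: 70 districts, K = 10 villages/wards per district, m = 40 people per village/ward, design effect 2, and a third-survey estimate of 24.1% (23.0 to 25.3). Assumed: equal weights, districts a random sample without stratification, and a district share of the village-level variance (or correlation) between 10% and 50%.

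**Basis 1: design effect of 2 taken as village-level.** The plan does not attribute the 2 to any stage, so this is an assumption.

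- Village as PSU: deff = 1 + (m − 1)ρc. Setting this to 2 gives ρc = 1/39 = 0.026.
- District as PSU: deff = 1 + (m − 1)ρc + (K − 1)mρd = 2 + 360ρd.
- SE ratio = √(district deff / village deff).
- Coverage of the village-based interval = 2Φ(1.96/ratio) − 1.

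At 30% prevalence and n = 28,000, the village-based half-width is 1.96 × √(2 × 0.21/28,000) = 0.76 points.

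| ρd as share of ρc | District deff | SE ratio | Correct half-width (points) | Coverage, formula | Coverage, simulated |
|---|---|---|---|---|---|
| 0% | 2.00 | 1.00 | 0.76 | 95% | 95.1% |
| 10% | 2.92 | 1.21 | 0.92 | 89.5% | 89.5% |
| 25% | 4.31 | 1.47 | 1.11 | 82% | 81.5% |
| 50% | 6.62 | 1.82 | 1.38 | 72% | 71.4% |

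The simulation is beta-binomial with 4,000 replicates per row. With district as PSU, the same runs gave 94.5% to 95.2% coverage.

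**Basis 2: third-survey interval, assumed village-based.**

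- SE = (25.3 − 23.0)/(2 × 1.96) = 0.587 points.
- Variance per village mean = 700 × SE² = 241.0. The binomial part is 24.1 × 75.9/40 = 45.7, which leaves 195.3 between villages.
- For district share s: SE² = 195.3s/70 + (241.0 − 195.3s)/700.
- s = 10%: SE² = 0.279 + 0.316 = 0.595, SE 0.77, ratio 1.31, coverage 86%.
- s = 50%: SE² = 1.395 + 0.205 = 1.600, SE 1.26, ratio 2.16, coverage 64%.

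**If stratification removed half the district variance (basis 2).** SE² becomes 195.3s/140 + (241.0 − 195.3s)/700.

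- s = 10%: SE² = 0.456, ratio 1.15, coverage about 91%.
- s = 50%: SE² = 0.902, ratio 1.62, coverage about 77%.

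**Ages 6-9 (m = 4).** Here the district term is 36ρd.

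- With ρc = 0.026, the ratio runs from √(1.169/1.077) = 1.04 to √(1.538/1.077) = 1.20.
- A second value of ρc comes from the third-survey interval. With n = 28,000 assumed, the simple-random SE is √(24.1 × 75.9/28,000) = 0.256 points. The design effect is then (0.587/0.256)² ≈ 5.3, and ρc = (5.27 − 1)/39 = 0.109. The ratio runs from √(1.719/1.327) = 1.14 to √(3.289/1.327) = 1.57.

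**The case against.** The strongest reply is that the plan leaves a detail out and does not state an error. The sentence on cluster sampling can be read to cover the whole multistage design, and Stata can take district as PSU. A reader might infer that the plan commits to villages alone and that the interval is bound to be too narrow. The text does not go that far. What remains is that the only unit the protocol calls a cluster is the village or ward, so the natural reading leads to the wrong stage.

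Second, the first stage is not described. In the introduction, random sampling is attributed to the clusters, not to the districts. If districts were drawn within strata, only the within-stratum district variance counts, and a district selected with certainty contributes none. This stands, and it reduces the size. Treating all 70 districts as fixed strata would justify village PSUs, but only for inference to those 70 districts, which is not the stated objective.

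Third, a reader might take the third survey's narrow interval as evidence that it was village-based. It is not. That interval also reflects weighting and assay adjustment, so it does not show which PSU was used. Nor do the city figures of 17.6% to 56% measure the spread between districts, since they come from separate city surveys at different times.

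Fourth, precision stays adequate. With ρc = 0.109, a 50% share and 30% prevalence, the district-based half-width is 2.68 points. That is still inside the 3 points implied by 10% of 30%, a target that the plan states for the age-group calculation. The weakness is therefore in the interval's coverage, not in the sample size.

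Fifth, one might conclude that comparisons between rounds are overstated in the same way. The rounds reuse the same districts, so persistent district effects partly cancel in a difference. Widening each round's interval separately could overstate the uncertainty about change.

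**Conclusion.** The point holds as a conditional one. As worded, the plan leads most naturally to 700 village/ward PSUs, and that would understate the national standard error if prevalence differs between districts. For an assumed district share of 10% to 50%, the correct standard error is 1.2 to 1.8 times the village-based one on the protocol's design effect, or 1.3 to 2.2 times on the third-survey back-calculation. Nominal 95% coverage would be roughly 90% to 64%.

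These figures rest on an assumed district share, equal weights, and unstratified random selection of districts. With no difference between districts the loss is nil. The headline ratios should not be carried over to small subgroups: at ages 6-9 the range is about 1.04 to 1.57. The change should be made before analysis, because it affects the main reported interval and needs no change to data collection.

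**What to change.** In Analysis plan, A] General population, replace the general reference to cluster sampling with an explicit design declaration:

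- District is the first-stage PSU, with the strata actually used to select districts.
- Any district selected with certainty is its own stratum, with its villages/wards as the PSUs there.
- Village/ward is the second stage elsewhere, and the sampling weights are named.
- Districts are not otherwise treated as fixed strata for national inference.
- The same declaration is used for the overall, adult, child and subgroup intervals.

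The plan should also say briefly how the 70 districts were selected, since the strata depend on it. For comparisons between rounds, analyse the rounds jointly with district as PSU, so that the covariance from reusing districts is kept.

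The main declaration costs a sentence or two of text and one line of survey set-up code. The joint analysis needs the earlier rounds' individual data with district identifiers. The price is wider reported intervals and fewer degrees of freedom: 70 districts minus the number of strata, hence 69 without stratification.

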## **Expected benefits**

The fourth population-based serosurvey will help us to determine the prevalence of SARS-CoV-2 antibodies at the community level. It would also provide a better understanding of the transmission dynamics of SARS-CoV-2 infection among various population-level demographics and health care workers. This would serve as an objective measure of the impact of second wave on the transmission of SARS-CoV-2 infection in the country. The survey also would provide an opportunity to estimate the proportion vaccinated for COVID-19 in the community level.

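### Round 4 counts positivity on either assay and labels it infection, with no estimate under earlier rounds' rules or by vaccination status, so it cannot by itself support a trend or second-wave statement

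*Combined protocol and SAP*

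**What the plan says.** The Analysis plan (A] General population) sets the round 4 rule: "We will define an antibody positive case as an individual whose sera tested positive on either of the two assays". The same section calls the resulting figure seroprevalence of infection and uses it for the infection-to-case ratio and the infection fatality ratio.

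The opening background section describes the earlier rounds differently. On round 3: "In the third serosurvey, prevalence was estimated based on the presence of both IgG antibodies against SARS-CoV-2 S1 protein of the receptor binding domain" together with N. On round 2: "in second serosurvey prevalence was based on IgG antibodies nucleocapsid (N) protein of SARS-CoV-2".

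The background gives the reason for repeating the survey: "Repeated cross sectional serosurveys conducted in the same geographical location provide estimates to monitor trends". Expected benefits goes further: "This would serve as an objective measure of the impact of second wave on the transmission of SARS-CoV-2 infection".

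The only step taken for comparability is a separate adult estimate using one randomly chosen adult per household. Every serum is run on both assays (Laboratory procedures) and vaccination details are recorded (Study procedures). The planned breakdowns cover age, sex, locality, occupation, symptoms, contact and testing history. They do not include assay or vaccination status.

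**The concern.** On the same sera, everyone positive on N, or on both assays, is also positive on *either*. Moving to *either* can therefore only leave crude positivity unchanged or raise it. Separately, a vaccinated person who was never infected can be S1-RBD positive in round 4, which was not possible in a survey done before vaccination began. Choosing one adult per household touches neither issue. Vaccine eligibility was confined to health care workers, frontline workers and adult age bands, so the adult estimate, the one built for comparison, carries most of any vaccine-induced positivity.

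At stake is how a rise from the round 3 figure of 24.1% would be read. Without a matched estimate, the unmatched headline becomes the default comparator, and part of the rise could be credited to second-wave transmission when it comes from vaccination or from the rule.

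**Working it through.** **1. The rounds side by side** (background, Study population, Analysis plan)

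| Round | Fieldwork | Ages | Positivity rule | Vaccination |
|---|---|---|---|---|
| 1 | 11 May-4 June 2020 | adults | not stated | before |
| 2 | 17 Aug-22 Sept 2020 | 10+ | N IgG | before |
| 3 | 18 Dec 2020-6 Jan 2021 | 10+ | *both*, ambiguous | before (rollout began 16 Jan 2021) |
| 4 | June-July 2021 | 6+ | *either* | 160 million with at least one dose by 29 May 2021 |

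**2. The plan's own figure.** n = 2 × 1.96² × 0.30 × 0.70 / (0.10 × 0.30)² = 1792.7, which reproduces the stated 1792. The planning values (30% prevalence, design effect 2) are therefore used below.

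**3. Sampling benchmark.** Round 3 SE = (25.3 − 23.0)/(2 × 1.96) = 0.59 points. Round 4 SE = 100 × √(0.30 × 0.70 × 2/28,000) = 0.39 points. Treating the rounds as independent, the 95% half-width of the difference is 1.96 × √(0.59² + 0.39²) ≈ 1.4 points.

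**4. Rule change at the stated assay performance.** Sensitivity is 100% for both assays; specificity is 99.90% (S1-RBD) and 99.6% (N). With independent errors, specificity is 0.999 × 0.996 = 0.995004 for *either* and 1 − 0.001 × 0.004 = 0.999996 for *both*. The crude gap is (1 − p) × 0.004992, or 0.35 points at p = 30% and 0.38 at 24.1%. Correct adjustment for test performance takes it to zero.

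**5. Rule change if true sensitivity is lower (assumed values).** True prevalence is held at 30% and the assays are independent. *Both* = 0.30ab, N = 0.30a and *either* = 0.30 × [1 − (1 − a)(1 − b)], where a is the sensitivity for N and b for S1-RBD.

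| a, b | Both | N | Either | Either − both |
|---|---|---|---|---|
| 95%, 98% | 27.9% | 28.5% | 30.0% | 2.0 |
| 80%, 95% | 22.8% | 24.0% | 29.7% | 6.9 |
| 60%, 95% | 17.1% | 18.0% | 29.4% | 12.3 |

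**6. Vaccine-induced S1-RBD antibody.** Added points = 100 × (V/B) × r × (1 − p). V = 160 million is from the background. Assumed: r = 50-100% of vaccinees gain S1-RBD but not N antibody; p = 30% already infected, unrelated to vaccination; base B = 1.0-1.4 billion.

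| B | r = 50% | r = 100% |
|---|---|---|
| 1.0 billion | 5.6 | 11.2 |
| 1.3 billion | 4.3 | 8.6 |
| 1.4 billion | 4.0 | 8.0 |

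The count of 160 million predates fieldwork and is cumulative, so it can only have grown. The addition shrinks in proportion to 1 − p if more people were already infected.

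**7. Age extension.** Ages 6-9 make up 2,800/28,000 = 10% of the sample. If their prevalence is 5-20 points lower (assumed), the pooled 6+ figure moves by 0.5-2.0 points. Adult and age-specific figures do not move.

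**The case against.** The strongest reply is that the objectives concern current antibody prevalence in children, adults and health care workers, and that no between-round difference, test or trend model is specified. The plan also acknowledges vaccine-induced antibody, records vaccination and will estimate coverage. All of this is correct: trend and second-wave impact are stated purposes, not specified analyses, and no listed objective fails. But the comparability step shows that comparison is intended, and Expected benefits states the second-wave claim outright.

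Three stronger readings are tempting, and the documents do not support them.

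- A reader might infer that round 3 required positivity on both assays, so that the rule change alone inflates the rise by many points. The sentence can equally mean that two antibodies were measured in round 3 where round 2 measured one. On that reading the rule may not have changed between rounds 3 and 4. Round 2 would still differ, but the second wave is dated from February 2021, so its natural contrast is round 3 to round 4.
- A reader might take the 2-12 points in step 5 as the expected artefact. They need sensitivities below the stated 100%, and the documents give none.
- A reader might infer that the wider age range spoils comparison generally. Adult and by-age estimates are planned, so only the pooled 6+ figure is affected. What is missing is a named 10+ estimate, although infections are scaled to the population above 10 years.

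It is also fair to say that the documents do not state which antibodies either vaccine induces. The assumption in step 6 of S1-RBD without N is therefore open.

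**Conclusion.** The point holds in limited form. As written, the plan cannot separate new infection from vaccine-induced antibody, or from any change of positivity rule, and so does not support the second-wave statement in Expected benefits. This does not depend on how the round 3 wording is read, because even an unchanged *either* rule counts something new once vaccination has begun.

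The size is conditional. Vaccination adds roughly 4-11 points under the assumptions in step 6, against a sampling half-width of about 1.4. Assay discordance adds to that only if true sensitivity is below the stated 100%; at the stated values the gap is under 0.4 points crude and nil after adjustment. The age extension is minor. The *either* figure remains a sound estimate of current antibody prevalence. The change is a low-cost improvement to what can be concluded about infection and trend, not a repair of the primary objectives.

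**What to change.** 1. State in the background which rule round 3 used: positive on both assays, or on either.
2. Keep *either* as the headline, labelled as current antibody prevalence rather than infection.
3. Pre-specify four estimates: N positive whatever the S1-RBD result, S1-RBD positive whatever the N result, both, and either. Adjust each with the sensitivity and specificity that belong to that rule. Report them for adults and for ages 10+, overall and by vaccination status.
4. Base any between-round or second-wave statement on the estimate that matches the earlier round's rule and age range. Age-standardise any comparison that uses the unvaccinated: rollout went by occupation and then by descending age, so they are a selected, younger group. Standardising for age will not remove the selection by occupation, which should be acknowledged.

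The cost is analysis-plan wording and one extra table. No further testing or data collection is needed. The downside is that the like-for-like rise may look smaller than the headline.

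### The adult trend is labelled infection but will mix infection with vaccination since round 3, and no comparison with earlier rounds is specified for vaccine-ineligible 10–17-year-olds

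*Combined protocol and SAP*

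**What the plan says.** The Analysis plan, A] General population, contains one analysis motivated by comparison with earlier rounds. It begins "We will separately estimate the seroprevalence of infections only among the adults" and continues "In order to maintain comparability with the previous surveys, we will randomly select one adult survey participant per household from the survey database". The same section counts a participant as positive if either the N or the S1-RBD assay is positive. It also plans seroprevalence "by age, sex, locality, occupation, symptom status, contact history, RT-PCR testing and confirmation status", without naming age bands. Vaccination status is not in that list, although Study procedures records it.

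The opening background gives the rest of the picture:

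- Round 1 covered adults only. Round 2 covered ages 10 and above, and so did round 3: "ICMR conducted the third population-based serosurvey among individuals aged 10 years and above". Round 3 ran from 18 December 2020 to 6 January 2021.
- Vaccination started on 16 January 2021 with health care workers, then frontline workers, then age groups above 60 and above 45. The widest phase is the last: "And finally Phase 4 for all above 18 years of age began on May 1, 2021". No phase for under-18s is listed.
- The antibodies that such surveys measure are described as both natural and vaccine induced.
- Objective 1(a) is a single estimate for ages 6–17, and the background says that no earlier survey included children under 10.

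Sample size, A] General population, allots "5600 children in the age group of 10-17 years" and 2,800 aged 6–9. Expected benefits says of the survey: "This would serve as an objective measure of the impact of second wave", meaning its impact on transmission.

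**The concern.** The group chosen for the cross-round comparison is the only age group that gained vaccine antibodies between rounds 3 and 4. An either-assay positive does not separate a past infection from a vaccine response, yet the plan calls the adult result a seroprevalence of infections. Followed literally, it would count vaccine responders as infected in the one comparison it sets up, and the rise since round 3 would be read as the second wave.

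The survey also enrols a group without this problem. Ages 10–17 had no vaccine phase and were within the age range of rounds 2 and 3. The plan states no comparison for them, and the child objective pools them with 6–9-year-olds, so the pooled 6–17 figure has no predecessor. At stake is whether the survey can support the statement about second-wave transmission that it offers as a benefit.

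**Working it through.** **1. The plan's own sample size.** Inputs from Sample size, A]: p = 0.30, relative precision 10% (d = 0.03), 95% confidence, design effect (deff) 2.

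n = deff × 1.96² × p(1−p)/d² = 2 × 3.8416 × 0.21/0.0009 = 1,792.7. The stated 1,792 reproduces.

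The 10–17 quota is 70 districts × 10 clusters × 8 = 5,600, which is 5,600/1,792 = 3.1 times that requirement.

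**2. Precision of a 10–17 level in round 4.** Half-width = 1.96 × √(2 × 0.21/5,600) = 1.7 points at 30%. If one child per household cut the group to 2,800 (assumed), it is 1.96 × √(2 × 0.21/2,800) = 2.4 points, still inside the 3-point target.

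**3. Timing.** Round 3 closed ten days before the first vaccine dose, so round 3 contains no rollout antibodies in any age group and round 4 contains them in adults.

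**4. Size of the vaccine component in adults.** The documents give 160 million people with at least one dose on 29 May 2021. The adult population is not given; assume 850 million to 1 billion. Coverage v is then 160/1,000 = 16% to 160/850 = 19%.

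Lift = v × (1 − share already positive) × share of the rest who seroconvert. The last two inputs are assumptions:

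| Coverage | Already positive | Seroconvert | Lift (points) |
|---|---|---|---|
| 16.8% (950 million adults) | 70% | 70% | 3.5 |
| 16% | 50% | 50% | 4.0 |
| 17.8% (900 million adults) | 40% | 90% | 9.6 |
| 19% | 24.1% (round 3 level) | 90% | 13.0 |

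Taking the least favourable value of every input at once gives 0.16 × 0.3 × 0.5 = 2.4 points. If coverage reached 30% by fieldwork (assumed), the first and third rows' other inputs give 6.3 and 16.2 points.

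For scale, round 3's interval of 23.0–25.3% has a half-width of 1.15 points. That interval is for all ages 10 and above, not adults alone.

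**5. Precision of a 10–17 change from round 3 to round 4.** Half-width = 1.96 × √(deff × [p4(1−p4)/n4 + p3(1−p3)/n3]). From the plan, n4 = 5,600. Assumed: p3 = 0.25, p4 = 0.4–0.6, n3 = 2,800–5,600, deff 2–5.3. The upper deff is what round 3's interval implies if its n was 28,000: (0.0115/1.96)² ÷ (0.241 × 0.759/28,000) = 5.3.

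- Best case (deff 2, n3 = 5,600, p4 = 0.4): 1.96 × √(2 × 0.4275/5,600) = 2.4 points.
- Worst case (deff 5.3, n3 = 2,800, p4 = 0.5): 1.96 × √(5.3 × [0.25/5,600 + 0.1875/2,800]) = 4.8 points.
- If matching household selection also cut n4 to 2,800, with n3 = 2,800: 3.4 points (deff 2, p4 = 0.4) to 5.6 points (deff 5.3, p4 = 0.5).

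The formula treats the two rounds as independent.

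**The case against.** The strongest reply has four parts.

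- **Adults were chosen for a reason.** Round 1 was adults only, so adults are the one group measured in all four rounds. This stands, and it is why the adult series should stay. It does not justify the infection label or the absence of a second comparison.
- **The adolescent data are not ignored.** A reader might infer that they go unused. The documents do not support that: seroprevalence by age is planned, ages 10–17 have their own quota, and the sample is described as adequate for each age group. A 10–17 level may well be reported. What is missing is a named band and a stated comparison.
- **Other vaccine-free readings exist.** A reader might take ages 10–17 as the survey's only one. Ages 6–9 also had no vaccine phase, and unvaccinated adults can be identified. But ages 6–9 have no baseline. Unvaccinated adults are a selected group, because rollout followed occupation, age and comorbidity, and they have no counterpart in round 3. Ages 10–17 are unique only as a vaccine-ineligible age group with an earlier baseline.
- **A rise in adolescents is not infection alone.** That inference is tempting but does not follow. A change in prevalence is net of antibody loss. The positivity rule also moved: N only in round 2, described as presence of both antibodies in round 3, either in round 4. A looser rule can raise positivity without new infections.

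It is also fair that the objectives are antibody levels, not changes, and that the second-wave statement is an expected benefit rather than an estimand. Even so, the plan itself sets up an adult comparison across rounds and names it infection.

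**Conclusion.** The concern holds in a limited form. The adult change from round 3 to round 4 is infection plus vaccination, and the plan's wording treats it as infection. The vaccine part is roughly 3.5–13 points at the 29 May coverage. That rests on an assumed adult population, prior positivity and seroconversion; the range shows that the effect is material and does not estimate it. Even the 2.4 points from the least favourable inputs exceeds round 3's half-width of 1.15.

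Ages 10–17 can supply a change that vaccination does not affect, provided that the rule, weights and household selection match. That change would be net of waning and would describe adolescents only. Its 95% half-width of about 2.4–4.8 points depends on a round 3 adolescent sample size and prevalence that the documents do not give. This is worth correcting before analysis.

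**What to change.** In the Analysis plan, A] General population:

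1. Keep the adult series, but describe its round 3 to round 4 change as infection plus vaccination, not as infection.
2. Add wording such as: *Seroprevalence at ages 10–17 will be reported as a separate band. Its change from round 3 to round 4 will be given with a 95% CI, using the same weights, the same assay-positivity rule with its matching test-performance correction, and the same within-household selection in both rounds. This is the measure of change not affected by vaccination; it is net of antibody waning and is not to be transferred to adults.*
3. Report ages 6–9 separately as a first measurement, alongside the pooled 6–17 figure that objective 1(a) requires.

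Listing vaccination status among the seroprevalence breakdowns for adults would be a useful complement, with the selection caveat stated.

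The cost is a few lines of analysis text and one added comparison, with no new fieldwork. The real burden is that round 3 individual results may need re-analysis under the common rule, and household matching may reduce the adolescent sample. The sponsor should state round 3's 10–17 sample size so that the expected precision can be fixed in advance.
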